## Abstract

**Background:**

In Turkey, there are serious deficiencies in mental health care. Although depression is highly prevalent, only a small number of people seek professional help. Innovative solutions are needed to overcome this treatment gap. Web-based problem-solving therapy (PST) is an intervention proven to be effective in the treatment of depression, although little is known about its clinical effects in Turkey.

**Objective:**

This study aims to test the clinical effects of a Web and mobile app of an adapted PST for depressive symptoms among the general population in Turkey.

**Methods:**

Participants will be recruited through announcements in social media and the Middle East Technical University. Adults (18-55 years) with mild to moderate depressive symptoms (Beck Depression Inventory-II [BDI-II] score between 10-29) will be included in the study. Participants with a medium-to-high suicidal risk (according to the Mini-International Neuropsychiatric Interview) will be excluded. A 3-armed randomized controlled trial with a waiting control group will be utilized. A sample size of 444 participants will be randomized across 3 groups. The first experimental group will receive direct access to the Web version of the intervention; the second experimental group will receive direct access to the mobile app of the intervention as well as automated supportive short message service text messages based on PST. The control group consists of a wait-list and will gain access to the intervention 4 months after the baseline. The intervention is based on an existing PST for the Turkish population, *Her Şey Kontrol Altında* (HŞKA), consisting of 5 modules each with a duration of 1 week and is guided by a clinical psychologist. The primary outcome is change in depressive symptoms measured by the BDI-II. Secondary outcomes include symptoms of anxiety, stress, worry, self-efficacy, and quality of life. Furthermore, satisfaction with, usability and acceptability of the intervention are important features that will be evaluated. All outcomes will take place online through self-assessment at posttest (6-8 weeks after baseline) and at follow-up (4 months after baseline).

**Results:**

We will recruit a total of 444 participants with mild to moderate depressive symptoms from March 2018 to February 2019 or until the recruitment is complete. We expect the final trial results to be available by the end of May 2019. This trial is funded by the Scientific and Technological Research Council of Turkey (National Postdoctoral Research Fellowship Programme 2016/1).

**Conclusions:**

Results from this study will reveal more information about the clinical effects of HŞKA as well as its applicability in a Turkish setting through the Web and mobile platforms. On the basis of the results, a guided Web- and mobile-based PST intervention might become an appropriate alternative for treating mild to moderate depressive symptoms.

**Trial Registration:**

ClinicalTrials.gov NCT03754829; https://clinicaltrials.gov/ct2/show/NCT03754829 (Archived by WebCite at http://www.webcitation.org/74HugwLo7).

**International Registered Report Identifier (IRRID):**

DERR1-10.2196/13239

## Introduction

### Background

According to the Human Rights in Mental Health Initiative (RUSIHAK), mental health care in Turkey has serious deficiencies [1]. From 2011 to 2014, RUSIHAK monitored Turkey’s largest psychiatric hospitals and reported several problems. Among these are the undertreatment of mentally ill patients, a lack of psychologists, and inadequate psychosocial and rehabilitation options for patients and their relatives [1,2]. In Turkey, limited epidemiological studies are available; however, some studies revealed rates of depressive disorders ranging from 4.4% [3] up to 48.0% in the general population [4]. However, only 18% of these seek professional help during their lifetime [1]. Depression is one of the most common mental disorders worldwide [5].

The World Health Organization states that depression is the leading cause of disability globally [5]. It affects the quality of life considerably [6,7]; it is associated with impaired social relationships [8] and high economic costs [9,10]. Moreover, it is also associated with excess mortality rates [11].

Over the past decennia, several clinically effective treatments have been developed for depressive disorders, including antidepressant medication and psychotherapy such as cognitive behavioral therapy (CBT) [12-15]. However, not everyone who is in need of professional mental help receives adequate therapy in Turkey [1].

Innovative ways to overcome this treatment gap are electronic mental health (e-mental health) apps. E-mental health refers to the use of information and communication technologies for mental health, which are promising in several ways. The internet offers opportunities to target populations that are not sufficiently reached in other ways. Furthermore, self-management by the patient is encouraged, and the cost-effectiveness and delivery of treatments are increased [16]. As Turkey occupies fifth place among countries in Europe using the internet, with a penetration rate of 69.6% [17], and almost 84% of the Turkish population uses a smartphone [18], the internet could offer many benefits.

For approximately two decennia, Web-based treatments built on evidence-based face-to-face protocols, which are highly structured and guided, are being used [19]. These treatments have been found to be effective in the treatment of depression. The treatments include Web-based CBT [20] and problem-solving therapy (PST) [21]. The version of PST that is most examined as an internet-based intervention is based on self-examination therapy [22,23] and is aimed at teaching patients how to cope with solvable, unsolvable, and unimportant problems that cause depressive symptoms and determine the important things in life by a structured step-by-step method. By doing this, patients regain mastery of their problems in daily life, leading to a reduction in their depressive symptoms. However, only limited data on the effects of such interventions (either offered offline or online) in Turkish populations are available [24].

One randomized controlled trial (RCT) was conducted at the Vrije University in Amsterdam to test the clinical effects of a culturally adapted Web-based PST (originally developed by the VU University) *Her Şey Kontrol Altında* (HŞKA) for Turkish migrants with depression in the Netherlands [25]. A total of 287 people applied for the trial, but only 96 participants were included and randomized into 2 groups: 49 in the experimental group and 47 in the control group (wait-list). Results showed that there was no significant difference between the 2 groups concerning depression because of an underpowered sample. However, a high effect size was found at follow-up, suggesting possible effectiveness of the treatment in the longer term [25]. Furthermore, in a recent meta-analysis, it was found that PST is effective with small effect sizes across different populations and settings [21]. In addition, the internet can be also advantageous for several different purposes. To recruit participants, Facebook has been used in a Web-based intervention [25,26]. For example, Facebook has been used as part of the trial to reach Turkish migrants, which led to 3308 Friends on Facebook, of whom about 250 sent a direct message to the researcher [26], implying that the internet may be used to try to lower the stigma for seeking professional help for psychological problems. Electronic learning (e-learning) platforms can also be used for communicating about participants’ weekly exercises [24]. Videoconferencing can be applied as an efficient alternative to face-to-face therapy [27].

In 2014, the Vrije University in Amsterdam and Middle East Technical University (METU) in Ankara initiated a European scientific collaboration [28]. In a total of 11 European regions, computerized CBT and videoconferencing were evaluated and implemented in routine mental health care practices, with a minimum of 5230 patients with depression. The Web-based treatment HŞKA designed by the Vrije University, with the enhancement of a behavioral activation module, was used for the Turkey region. Initial results are encouraging regarding the reduction of depressive symptoms [24]. However, this intervention was provided through the student e-learning platform of the METU. This system was developed for coursework, in which users had to download and upload PDF or Word files to fulfill the exercise requirements of the Web-based therapy modules. For monitoring clients’ assessments and evaluations and to provide feedback, separate stand-alone software programs had to be used. Therefore, the overall suitability of an e-learning platform for Web-based PST was evaluated as low.

On another front, mobile health technologies may offer opportunities to boost the effects of psychological interventions [29]. For example, a recent study showed higher adherence in the experimental group who received CBT therapy with daily automated supportive messages on their smartphone compared with the control group who received CBT without these messages [30]. The addition of automated supportive short message service (SMS) text messages to Web-based interventions may be, therefore, potentially effective in monitoring patients and their adherence to treatment [30,31].

### Objectives

On the basis of our previous experience with HŞKA, we intend to start a new trial, because previous research has shown that computerized CBT is an effective way to reach and possibly to treat problems associated with mild to moderate depression [25,26]. In this trial, HŞKA as a stand-alone intervention will be used for 2 purposes. First, a compact Web and mobile app of the treatment will be developed and updated with pilot studies that evaluate the acceptance and usability of the intervention. Second, an RCT of the clinical effectiveness of the Web and mobile app will be conducted in the general population in Turkey.

## Methods

### Intervention Description

HŞKA was previously culturally adapted and tested for clinical effectiveness in Turkish migrants in the Netherlands [25,32]. The cultural adaptation consisted of language, the use of culture-specific cases and problems according to the worldview of the Turkish target group, and culture-specific examples of persons with similar problems. The intervention was translated from Dutch into Turkish, and it was adapted in terms of cultural sensitivity.

Cultural adaptation of psychotherapy has been defined as the modification of intervention protocols according to clients’ values, contexts, and worldviews [33]. Culture-specific adaptations in this intervention included several components: first, the participants’ native language; second, description of psychological problems in terms of idioms of distress (eg, using symptoms of depression instead of the term depression); third, explicit discussion of migration and culture by using culture-specific cases and problems that are recognizable for the target group concerned; and finally, inclusion of recognizable examples of persons with similar problems (eg, a young woman who migrated 2 years ago and cannot find her way in the Netherlands). For the purpose of this study, migration-related adaptations were removed, and the language was checked again by a native speaker.

HŞKA consists of 5 modules over 5 weeks, consisting of text, photos, videos, and exercises. Briefly, the length of each module is 1 page and the duration of videos 2 to 3 min. First, participants indicate what they think is important in their lives; they make a list of their problems and worries, and they categorize their problems into 3 groups: (1) unimportant problems, which are not related to what they think is important in their lives; (2) important but solvable problems, which are tackled with a systematic, problem-solving approach consisting of 6 steps (which consists of defining the problem, developing alternative solutions, choosing the best solution, making a plan for the solution, implementing the solution, and evaluation); and (3) important but unsolvable problems, such as having lost someone through death or having a chronic physical illness and making a plan for how to live with it. Each session includes about 1.5 A4 pages long text with explanations and examples and short videos about the theory; at the end of each session, exercises can be made. The core of the intervention is the 6-step problem-solving procedure, which teaches users this technique for several of their important but solvable problems. The idea is that by mastering this technique, people will regain mastery of their problems and ultimately their lives. Participants receive feedback on their homework assignments in brief weekly online messages from a clinical psychologist with a PhD degree in Clinical Psychology (first author). Those who have not sent their assignments will receive a reminder within the app once a week. After 3 reminders, participants who still have not sent anything will be considered as dropouts.

This project consists of 3 phases (Figure 1). In the first phase, the content of the existing intervention HŞKA for depressive symptoms will be used to develop a compact Web app. In the second phase, the content of the Web-based intervention will be used to develop a mobile app. In both of these phases, pilot studies will be conducted to optimize the software apps to find and resolve software errors. In this last phase, the final version of the Web and mobile apps will be used to perform an RCT with 3 arms. Screenshots of the interventions are provided in Multimedia Appendices 1-3 [34]. The first experimental group will receive direct access to the Web version of the intervention; the second experimental group will receive direct access to the mobile app of the intervention and will also receive daily automated supportive SMS text messages based on PST once a day for 2 months. The content in the daily notifications is derived from the content of the modules, for example, “Once a week, take a birds-eye view of your life to evaluate it.” The rationale behind using notifications in the mobile app is to avoid dropouts as indicated [30,31]. Adding notifications for the Web version does not make it equal to the mobile version because the users who use the Web version only see the notifications if they decide to log in, whereas the users of the mobile version see the notifications when a flag appears on their main screen. The control group consists of a wait-list and will receive the treatment after the study has been finished. A flow chart of the RCT is presented in Figure 2. Ethical approval for the RCT study has been obtained from the Human Subjects Ethics Committee of METU (No. 28620816/21).

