### Sample Size

In this RCT, 2 experimental groups (receiving the intervention by either the internet or a mobile app) will be compared with a waiting list control group. The sample size is calculated based on an expected difference of Cohen *d*=0.45 (moderate) between 1 of the experimental groups and the control group as in previous studies [22,25]. “ *F* tests-analysis of variance repeated measures” will be applied in G-Power Statistical Power Analysis program version 3.1 and used for sample size calculation [55]. To obtain a power of .80 for a 1-tailed test and an alpha of .05, a total of 234 participants for 3 groups is needed. However, high attrition rates at posttest (25.0%) and at follow-up (30.0%) are expected based on previous studies [24,25]. Therefore, the sample size will be increased to 444 participants in total (allowing an attrition of 25.0%*30.0%=52.5%). This means that 148 participants are required at baseline for each group.

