### Statistical Analyses

The study will be reported in accordance with the consolidated standards of reporting trials guidelines [57]. The data obtained from the study will be evaluated and data tables created using the Statistical Package for Social Sciences version 25.0 statistical software program [58]. The significance level will be accepted as 95% CI (*P*<.05) in all statistical analyses. Quantitative (categorical) variables will be expressed as mean, SD, and upper and lower values in this study, whereas qualitative (continuous) variables will be expressed as numbers (n) and percentage (%). The Kolmogorov-Smirnov Test will be used to examine whether the quantitative data were distributed normally. To measure the efficacy of the treatment in this study, general linear model repeated measures analysis will be used to investigate the change on the primary outcome (BDI-II) scores in dependent variables for the total sample based on the intention-to-treat principle and for analyzing missing data [59]. McNemar tests will be used to measure categorical change as a version of the Chi-square test of independence in repeated measures of dependent groups. Furthermore, the Fisher exact Chi-square tests will be used if the number of crosstabs data is insufficient and the hypothesis is not achieved. Attrition will be defined as not completing any or 1 of the posttreatment measures. The notification effect will be analyzed by comparing the dropout rates of the Web and mobile versions. Finally, the correlation coefficient and statistical significance between the quantitative variables will be calculated by 2-way Pearson correlation analysis.

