### Limitations

Although online guided self-help for depressive symptoms is promising, there are some points to consider. First, in a previous study among Turkish migrants with depressive symptoms, the sample size was not large enough to detect a small to moderate effect [25]. Recruitment was difficult, and the suicidal risk was moderate to high in the same study. It is expected that the same difficulties will be encountered during this trial. Second, attrition is generally high in online intervention trials and can be more than 50% [63,64]. In the study of Ünlü Ince et al [25], attrition was even higher, which led to missing data. It is expected that attrition in this study will be comparable with that of online intervention studies; however, the daily automated notifications in the mobile experimental group may counteract such high attrition rates. Finally, this study will only evaluate the severity of depressive symptoms, which means it will not be possible to say anything about recovery from a depressive disorder.

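### The design expects more complete BDI-II data in the mobile arm, but the stated model does not by itself handle missing scores and no sensitivity analysis covers unequal loss

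*Protocol article*

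**What the plan says.** All of this is in the Protocol article.

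- **Intervention Description.** The mobile arm "will also receive daily automated supportive SMS text messages based on PST once a day for 2 months". The reason given is: "The rationale behind using notifications in the mobile app is to avoid dropouts as indicated [30,31". Neither the Web arm nor the wait-list gets these messages.
- **Limitations.** After noting that high attrition caused missing data in the earlier trial in Turkish migrants, the authors write that "the daily automated notifications in the mobile experimental group may counteract such high attrition rates".
- **Sample Size.** The target is a Cohen d of "0.45 (moderate) between 1 of the experimental groups and the control group". "To obtain a power of .80 for a 1-tailed test and an alpha of .05, a total of 234 participants for 3 groups is needed". Then "high attrition rates at posttest (25.0%) and at follow-up (30.0%) are expected based on previous studies", with no split by arm. The total is raised to 444: "This means that 148 participants are required at baseline for each group".
- **Statistical Analyses.** A general linear model for repeated measures, in SPSS, is the analysis of BDI-II change in the whole sample by intention to treat, and the same sentence gives it the task of dealing with missing data, with a citation. No imputation method, missing-data assumption or sensitivity analysis is named. On dropout: "The notification effect will be analyzed by comparing the dropout rates of the Web and mobile versions".
- **Per-Protocol Analysis.** The set of participants with all measurements and all modules is secondary.

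**The concern.** A feature meant to keep people in the trial is given to one arm. If it works, BDI-II will be missing less often, and for different people, in the mobile arm than in the other two. The mobile-versus-control and mobile-versus-Web contrasts would then compare groups filtered to different degrees after randomisation.

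The direction depends on who leaves. If the more depressed leave, the heavily filtered wait-list looks too well and the mobile effect is understated. If those who have improved leave, it is overstated. The documents do not say which is likelier.

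The model named does not settle this. The repeated-measures general linear model needs a score at every time point, so without imputation it discards anyone who missed one. The intention-to-treat label does not change which rows enter the fit. With nearly half the sample expected to be lost by follow-up, that matters.

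**Working it through.** **1. The plan's own figures.** With 25% lost by posttest and a further 30% by follow-up, retention is 0.75 × 0.70 = 0.525, so attrition is 47.5% (the Sample Size section labels the 52.5% as attrition). 234 / 0.525 = 445.7, or 446, against the stated 444; 444 × 0.525 = 233.1 retained. Per arm, 148 × 0.525 = 77.7. The 234 matches 3 × 78 from a two-sided 5% comparison at d = 0.45: 2 × (1.960 + 0.842)² / 0.45² = 77.5, or 78. The one-tailed test named in the text would need 62 per arm, 186 in all. Two-sided 5% is used below.

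**2. Mobile retention (assumed; no arm-specific rate is given).** The messages stop at 2 months, about when posttest falls. If they act only until then, the 30% later loss still applies.
- Messages halve the posttest loss: 0.875 × 0.70 = 0.6125.
- Messages abolish it: 1.00 × 0.70 = 0.70, the ceiling.

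Web and wait-list are held at 0.525.

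**3. Bias in a completer contrast.** Let staying depend on a normal latent variable with correlation ρ to BDI-II. The completers' mean shifts by ρ × φ(z)/r in SD units, where r is retention and z = Φ⁻¹(1 − r). The factor φ(z)/r is 0.758 at r = 0.525, 0.625 at 0.6125 and 0.497 at 0.70. The bias is ρ times the difference between arms. ρ is assumed.

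| Mobile retention | Difference in factor | ρ = 0.2 | ρ = 0.3 | ρ = 0.4 |
|---|---|---|---|---|
| 61.25% | 0.133 | 0.027 | 0.040 | 0.053 |
| 70% | 0.262 | 0.052 | 0.079 | 0.105 |

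Against 0.45 this runs from 0.027/0.45 = 6% to 0.105/0.45 = 23%. At ρ = 0 it is zero.

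**4. Consequence for mobile versus control.** SE = √(1/n_mobile + 1/77.7). With b the bias, type I error is Φ(−1.96 + b/SE) + Φ(−1.96 − b/SE), and power when the bias works against the mobile arm is Φ((0.45 − b)/SE − 1.96).
- Smallest case (n_mobile = 148 × 0.6125 = 90.65, SE = 0.155, b = 0.027): type I error 5.3%; power 78%, against 83% without bias.
- Largest case (n_mobile = 148 × 0.70 = 103.6, SE = 0.150, b = 0.105): type I error 10.7%; power 63%, against 85% without bias.

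**5. Does the common attrition rate cost power?** No. Unbiased power is 0.80 at equal retention, 0.83 at 61.25% and 0.85 at 70% mobile retention.

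**6. The planned Web-versus-mobile comparison.** With 148 per arm and 47.5% Web attrition, its power is 0.25, 0.59 and 0.87 for mobile attrition of 40%, 35% and 30%. A non-significant result would not rule out a difference, and the wait-list is not examined.

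**The case against.** The strongest reply is that this is detail for an analysis plan that is not shown. The primary analysis is intention-to-treat on the whole sample, the completer set is secondary, and the cited missing-data reference cannot be read here. A reader might infer that the mobile contrasts certainly rest on completers; the text does not establish that, since imputation may be specified elsewhere. What remains is that the article does not merely leave missing data open. It assigns them to a model that does not handle them unaided, in a design that expects unequal loss.

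Other replies limit the point:

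- Dropout in the Intervention Description means assignments not sent after three reminders, whereas attrition in the Statistical Analyses means measures not completed. Fewer of the first need not mean fewer missing BDI-II scores. The Limitations section does make the link to attrition, but only as a possibility.
- The arithmetic uses raw completer means and ignores baseline and posttest BDI-II. A model using those scores could remove part of the bias.
- Mobile retention of 75% at follow-up would give a bias up to 0.13 SD. That requires the messages to cut loss after they stop: 0.75 / 0.70 = 107% posttest retention is impossible, so the figure is not used.
- A reader might infer that there is no arm-specific check at all. There is one, between Web and mobile; its gap is the wait-list.

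**Conclusion.** The point holds as a modest and inexpensive improvement. The article builds in and foresees lower attrition in one arm, names a model that uses only complete cases unless values are imputed, and describes nothing that would show how far the mobile contrasts depend on who stayed. If complete cases are used, the bias is about 0.027 to 0.105 SD, of unknown sign. This rests on an assumed ρ of 0.2 to 0.4, assumed mobile retention of 61% to 70%, and 52.5% retention in the other arms. If leaving is unrelated to BDI-II there is no bias.

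Two stronger inferences are not supported. The single attrition rate in the Sample Size section is not a defect on this ground, because better mobile retention raises power. Nor does anything show that assessment invitations differ by arm: the weekly in-app reminder concerns assignments, and the payment for completing all three assessments is not limited to one arm.

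**What to change.** In the Statistical Analyses section:

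1. Analyse all randomised participants with every available BDI-II score, for example with a likelihood-based mixed model for repeated measures, and state its missing-at-random assumption.
2. Add a delta-adjusted sensitivity analysis of each active-versus-control BDI-II contrast, with delta varying separately by arm. This is needed as well because the mixed model does not protect against leaving that depends on the unseen score.
3. Report that result beside any mobile effect claimed.
4. Extend the attrition comparison to all three arms, counting missing BDI-II assessments separately from unsent assignments.

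The cost is some protocol wording and a little more analysis. The downside is that the mobile result may have to be reported as less certain. Neither the sample size nor the assessment invitations need to change on this account.
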